The HomeHealth service was tested in a feasibility randomised controlled trial (RCT) compared to treatment as usual (TAU, usual GP care), in which we recruited 51 older people with mild frailty from four UK general practices, 26 of whom received the intervention. The study successfully recruited within the expected timeframe, with 96% participants remaining in the study at 6 months and minimal missing data (< 1%) [33]. Our process evaluation indicated that the intervention was well-received according to participant interviews and a survey [40], feasible to deliver and had 91% attendance rates for appointments. The service was delivered at modest cost (£307—equivalent $417/patient in Feb 2022). At 6 months we found significantly better functioning (Barthel Index; + 1.68, p = 0.004) and grip strength (+ 6.48 kg, p = 0.02), reduced psychological distress (GHQ-12; -3.92, p = 0.01) and increased capability-adjusted life years (+ 0.017, p = 0.03) in the intervention arm compared to treatment as usual. There were no differences in other outcomes. Given the promising nature of the intervention, we aim to test the effectiveness and cost-effectiveness of HomeHealth in a definitive trial across a wider range of participants, providers and contexts.

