### Sample size

We are aiming to recruit a sample size of 386 people (193 per arm). This will provide 90% power at the 5% significance level to detect a minimum clinically important difference of 1.85-points [72] in the BI, with a standard deviation (SD) of 5. We found a SD of 3 in the feasibility RCT, however in frail populations larger SDs have been reported [20, 22] so we have conservatively assumed a larger SD. Using 90% power and 5% significance level, this would require 308 people (154 per group). Attrition was minimal (6%) over 6 months in our feasibility study, however other studies have reported higher attrition rates with longer follow-up [8] so we have conservatively assumed 20% attrition over 12 months. The first six months will form a pilot phase based on site-specific and overall recruitment rates (target red < 80, amber 80–159, green 160 +), with measures put in place if we are not recruiting at ‘green’.

We have not adjusted for clustering by therapist (HomeHealth worker) as we anticipated that this will be minimal and non-significant. No trials in those with mild frailty have reported intraclass correlation coefficients (ICCs) for therapist clustering, only clustering by GP practice in cluster RCTs in older community-based general populations [73]. Unpublished PhD thesis data examining therapist effects in a secondary analysis of a cluster exercise trial in older people [74] did not find significant clustering by therapist (ICC 0.01, *P* = 0.54).

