### Statistical methods

A detailed statistical analysis plan, including the health economic analysis, will be developed a priori and reviewed and approved by the Trial Steering Committee. All analyses will be by intention to treat. As missing data in the feasibility study were low and there are few gains to multiple imputation in RCTs [75, 76], imputation will not be used. We will descriptively summarise participants’ baseline characteristics using appropriate summary statistics (mean and SD, median and interquartile range or proportions) by randomised group.

The primary outcome (BI score at 12 months) will be analysed using linear mixed models, including 6 and 12-month data, controlling for baseline BI score and site (the stratification variable). Assumptions will be checked and appropriate transformations or analogous models will be used if the assumptions of linear models are violated. The ICC will be reported. Continuous secondary outcomes will be analysed using similar linear mixed models to the primary outcome, including 6 and 12-month data and controlling for outcome baseline score and site. Dichotomous outcomes (death and exhaustion) will be analysed using logistic regression. Falls will be analysed using Poisson regression or an analogous alternative if the assumptions for Poisson are not met. If it is not possible to use Poisson regression or an analogous alternative, then we will consider dichotomising falls and analysing in a similar way to other dichotomous outcomes. If there are too few events to perform statistical modelling for falls or the other dichotomous outcomes, they will be reported descriptively.

We will examine baseline predictors of missingness for the primary outcome and include any significant predictors of missingness in a supportive analysis to restore the missing at random assumption using a similar model to the primary analysis. All analyses will be complete case. We will also perform a complier average causal effects (CACE) analysis after unblinding using a threshold dosage of 3 + sessions for compliance to determine the average treatment effect of participants who would have adhered to the protocol regardless of how they were randomised.

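### The unqualified complete-case rule conflicts with the two-visit mixed model and, carried into the economic analysis, drops partial completers from the cost-per-QALY result

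*Protocol article*

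**What the plan says.** All of the rules stand in the protocol article under Statistical methods.

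- Population: "All analyses will be by intention to treat".
- Primary model: the primary outcome, 12-month BI, "will be analysed using linear mixed models, including 6 and 12-month data, controlling for baseline BI score and site (the stratification variable".
- Imputation is ruled out, with two reasons given: "As missing data in the feasibility study were low and there are few gains to multiple imputation in RCTs [75, 76], imputation will not be" (last word of the sentence omitted).
- Supportive analysis: the trial will "include any significant predictors of missingness in a supportive analysis to restore the missing at random assumption using a similar model to the primary analysis".
- General rule, directly after the supportive analysis: "All analyses will be complete case". The term is not defined and no exception is given.
- Economic analysis: missing data are to be handled as in the statistical analysis. QALYs are an area under the curve from EQ-5D-5L, which Table 1 schedules at baseline, 6 and 12 months.

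The Sample size section says "we have conservatively assumed 20% attrition over 12 months". For the feasibility trial of 51 people, Background reports 96% retained at 6 months, while Sample size reports 6% attrition over the same period. The two figures differ slightly, so 4-6% is used below.

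**The concern.** A likelihood-based mixed model with two follow-up visits uses every observed outcome. A participant with a 6-month BI and no 12-month BI still informs the 12-month comparison, through the correlation between visits. Under missing at random this is a main reason to include the 6-month visit. A rule that all analyses use complete cases takes that away. It also sits badly with an unqualified intention-to-treat statement, because randomised people with usable outcome data are left out.

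Frail older people may well be lost because function has declined since baseline. If so, completers are a selected group, and the selection can differ by arm. Inflating the sample size for attrition protects power but does nothing about this bias. In the economic analysis no repeated-measures outcome model is described that would recover people with one visit missing, so the rule bites there whichever way the phrase is read.

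**Working it through.** **1. The plan's own figure.** Inputs from Sample size: difference 1.85, SD 5, power 90%, 5% significance (taken as two-sided).
n per arm = 2 × 5² × (1.960 + 1.282)² / 1.85² = 50 × 10.51 / 3.42 ≈ 153.5, so 154 per arm and 308 in all. With 20% attrition, 154 / 0.80 = 192.5, so 193 per arm and 386 in all. Both figures reproduce. With 154.4 per arm left, power is 90.2%. The 20% is therefore built into N.

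**2. Feasibility loss against planned loss, out of 386.**
- 4-6%: 386 × 0.04 = 15 to 386 × 0.06 = 23 people.
- 20%: 386 × 0.20 = 77 people.

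**3. Who is dropped on the literal reading.** Assume that nobody lost by 6 months returns, and that 4-12% are lost by then. The lower part of that range is the feasibility experience; the upper end is an assumption.
- With a 12-month BI: 386 × 0.80 = 309.
- With at least a 6-month BI: 386 × 0.96 = 371 down to 386 × 0.88 = 340.
- 6-month data discarded: 386 × (0.20 - 0.04) = 62 down to 386 × (0.20 - 0.12) = 31. At 6% lost by 6 months it is 386 × 0.14 = 54.

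**4. Illustrative bias in the 12-month effect.** Simulated trials had 193 per arm, SD 5, a true effect of 1.85 at both visits, 20% dropout, all of it after 6 months, and 3,000 runs per scenario. Where dropout depended on function, its log-odds rose by 1.5 for each SD by which 6-month BI was lower. Complete case is a baseline-adjusted comparison of those with 12-month BI. Likelihood is the two-visit estimate from all observed data. Monte Carlo error is about 0.49 / √3000 = 0.01.

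| Correlation: baseline with follow-up / 6 with 12 months | Dropout | Complete case | Likelihood |
|---|---|---|---|
| 0.5 / 0.5 | unrelated to outcome | -0.01 | -0.01 |
| 0.5 / 0.5 | low 6-month BI, both arms | -0.09 | 0.00 |
| 0.5 / 0.5 | low 6-month BI, control only | -0.32 | 0.015 |
| 0.5 / 0.7 | unrelated to outcome | 0.01 | 0.01 |
| 0.5 / 0.7 | low 6-month BI, both arms | -0.16 | 0.00 |
| 0.5 / 0.7 | low 6-month BI, control only | -0.62 | -0.02 |
| 0.7 / 0.8 | unrelated to outcome | 0.00 | 0.00 |
| 0.7 / 0.8 | low 6-month BI, both arms | -0.12 | 0.00 |
| 0.7 / 0.8 | low 6-month BI, control only | -0.43 | 0.00 |

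A second set used 1,500 runs per scenario, correlations of 0.75 (baseline-6), 0.70 (baseline-12) and 0.80 (6-12), and retention of 72-74% in control and 83-86% in intervention. Complete-case estimates were 1.73 and 1.70 against a truth of 1.85 (bias -0.12 and -0.15), and -0.19 against a truth of 0. The likelihood estimates were 1.86, 1.84 and -0.03.

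**5. QALYs.** An area under the curve over 12 months needs EQ-5D-5L at all three visits. At 20% attrition, 77 people lack the last one. Anyone who misses only the 6-month visit is added to that number; any deaths scored at zero utility are taken off it.

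**The case against.** The best defence is that complete case here may only mean observed data without imputation. The model names both visits, and the supportive analysis is framed in terms of missing at random. On that reading nobody with a 6-month BI alone is dropped from the primary model, and steps 3 and 4 do not apply to it. This is plausible. But the sentence covers all analyses and does not say so, which leaves two different primary analysis sets open. The reading also gives no relief to QALYs and costs.

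Four stronger conclusions might be drawn, and the document does not support them.

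- *That ruling out imputation contradicts the mixed model or intention to treat.* It does not. A likelihood model needs no imputation under missing at random, and people can be analysed as randomised without it.
- *That the no-imputation rule rests on under 1% missing data.* Statistical methods says only that missingness was low, and adds a second reason, the limited benefit of multiple imputation in trials. That reason rests on cited sources that cannot be checked here. The under-1% figure is in Background, separate from retention; the like-for-like contrast with 20% is 4-6%. The 20% is itself described as conservative.
- *That the 12-month result will be biased.* The correlations, dropout mechanisms and differential retention are assumptions. The SD of 5 is the planning value; the feasibility SD was 3. In these scenarios the material bias runs against the intervention.
- *That the lack of sensitivity analyses departing from missing at random, or of a rule for deaths, is an error.* The article defers detail to an analysis plan, which may contain them.

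**Conclusion.** The point holds in a limited form. The sentence as written conflicts with the primary model and fits poorly with intention to treat. Followed literally, it discards 6-month data on about 31 to 62 of 386 people. If dropout follows 6-month function, the cost is roughly -0.1 to -0.2 points, or 5-10% of the 1.85-point target (0.09 / 1.85 to 0.19 / 1.85). It reaches -0.32 to -0.62 (17-34%) only under strongly arm-specific dropout. The size depends on the assumed timing and mechanism of loss, and putting all loss after 6 months favours the likelihood model.

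Two parts do not depend on how the phrase is read. First, low missingness over 6 months in 51 people is weak support for a rule in a trial that plans for 20% loss over 12 months. Second, the rule as extended to QALYs and costs removes about 77 people from the primary cost-per-QALY analysis. The supportive analysis does not close the gap: it adds baseline predictors only, chosen by significance, and cannot "include any significant predictors of missingness in a supportive analysis to restore the missing at random assumption" if loss depends on function after baseline.

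**What to change.** 1. Replace the complete-case sentence with: *All randomised participants with baseline BI and at least one follow-up BI contribute, as randomised, to the likelihood-based mixed model under missing at random, without imputation.* Use matching wording for the continuous secondary outcomes.
2. Limit the no-imputation rule to the outcomes analysed by mixed model, and rest it on the model's use of all observed data rather than on feasibility missingness.
3. Give QALYs and costs their own rule, using a method that keeps partial completers under missing at random, for example multiple imputation by arm.

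This costs a change of wording and some extra analysis work for the economic evaluation. It needs no new data and leaves the sample size as it is. A delta-adjusted analysis of missing 12-month BI, and one that handles deaths explicitly, would be useful additions to the analysis plan, but they are optional.

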### Intervention

A detailed breakdown of the HomeHealth service is provided according to the TIDIER checklist [41] in supplementary file 1. HomeHealth is delivered over approximately six appointments in the older person’s home. Three appointments is considered a minimum dose, whilst participants could receive up to a maximum of 12 if they have particularly complex needs. These were originally planned to be delivered face-to-face with some telephone interim support, however they were adapted to be delivered by phone or video call, as needed, in light of the Covid-19 pandemic. If needed, internet-enabled tablets can be offered to participants receiving the intervention remotely to facilitate communication.

HomeHealth follows an intervention manual. In the first appointment, a HomeHealth worker comprehensively assesses the person, with a particular focus on socialising, mobility, nutrition and psychological wellbeing (including mood and memory), but including any other relevant issues (e.g. pain, continence, caring). Participants are encouraged to identify an outcome goal for the service that is important for them, and at either the first or second appointment are encouraged to break this down into behavioural goals, which are then operationalised into SMART (specific, measurable, achievable, relevant, timely) goals that are achievable in small steps over the course of the intervention. Goals can include a range of activities, such as home-based exercises based on the Otago programme (which shows effectiveness at reducing falls [42] and improving balance [43]), identifying social activities to attend or making dietary changes to improve protein or calorie intake. The COM-B model [37] is used by the HomeHealth worker to assess capability, opportunity and motivation to achieve the behavioural goal and to identify any barriers, developing an action plan with the person as to how these might be overcome. These are documented on a Health and Wellbeing Plan, and self-monitoring forms (e.g. diaries) may be used to record completion of activities such as exercises. Where relevant, equipment (e.g. weights or resistance bands) or information resources (e.g. details of local social groups) is provided to the older person.

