For the process evaluation, we will carry out a number of exploratory analyses, including whether those who get a therapeutic dose of HomeHealth (3 + sessions) have higher BI at 12 months; whether choice of goal impacts on related outcomes (e.g. social goal and UCLA-3 score) and whether progress towards goals is associated with higher BI scores. If sufficient data are available, we will explore the impact of remote delivery vs. face to face delivery on outcomes. We will descriptively summarise service delivery data (e.g. appointments attended) and compare the demographics of those recruited to the expected population to assess intervention reach. Qualitative data will be analysed using codebook thematic analysis [77], involving multiple multidisciplinary team members (including Patient and Public Involvement and Engagement (PPIE)), and barriers and facilitators to implementation will be explored using Normalisation Process Theory [78].

For the health economic analysis, we will calculate the mean incremental cost per quality adjusted life years gained (QALYs) using EQ-5D-5L and the relevant UK tariff. QALYs will be calculated from the EQ-5D-5L as the area under the curve adjusting for baseline [74] with site as a fixed effect in line with the analysis of the primary outcome. We will also report Years of Full Capability (YFC) using ICECAP-O and its respective tariff for the duration of the trial. YFC will be calculated according to the most current guidance [79]. The primary analysis will be the incremental cost per QALY gained from a health and personal social services cost perspective, with secondary analyses reporting the incremental cost per YFC gained, and calculating incremental costs from a wider cost perspective to capture the impact on carers and any patient/carer out of pocket costs for health and social care. Means and 95% confidence intervals will be based on bootstrapped results. We will adjust difference in total cost at 12 months by baseline values [80] with site as a fixed effect and a random effect for therapist clustering.

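### The CACE names a single cut at 3+ sessions, which assumes that one or two sessions do nothing; a supportive 1+ session CACE would bracket the complier effect

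*Protocol article*

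**What the plan says.** Under Statistical methods, the protocol article adds a CACE analysis, run after unblinding, to the intention-to-treat analysis. Compliance is defined "using a threshold dosage of 3 + sessions for compliance", and the aim is "to determine the average treatment effect of participants who would have adhered to the protocol regardless of how they were randomised". No other cut is named, and the estimator is not described.

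The cut has a stated basis. The Intervention section says: "Three appointments is considered a minimum dose, whilst participants could receive up to a maximum of 12". The process-evaluation analyses use the same cut and ask "whether those who get a therapeutic dose of HomeHealth (3 + sessions) have higher BI at 12 months". The usual course is about six appointments.

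The Intervention section also says what happens early. "In the first appointment, a HomeHealth worker comprehensively assesses the person, with a particular focus on socialising, mobility, nutrition and psychological wellbeing". Participants are encouraged to choose an outcome goal and "at either the first or second appointment are encouraged to break this down into behavioural goals", which are then made into SMART goals. Later appointments review progress and change or extend the goals. Action planning, equipment and information resources are described without an appointment number.

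**The concern.** A CACE with a binary cut divides the whole difference between arms by the share at or above the cut. This recovers the effect in compliers only if being allocated to HomeHealth does nothing for those below the cut (the exclusion restriction). Below three sessions there are two different groups: people who never started, for whom no effect is plausible, and people who had one or two sessions. By the article's own account the second group may already have had a full assessment and set goals. Any effect in them is credited to the people with three or more sessions.

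The CACE is the planned randomisation-based estimate of what HomeHealth does for people who take it up. The exploratory process-evaluation analysis of dose does not fill the gap: it uses the same cut and, as described, looks at those who got the dose.

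**Working it through.** **Figures in the plan.** The article gives no figure for the CACE, for the share reaching three sessions or for the share with one or two. The Sample size section supplies a scale: a difference of 1.85 Barthel points, SD 5, 5% significance (taken as two-sided), 90% power. These reproduce: 2 × (1.96 + 1.28)² × 5² / 1.85² ≈ 153.5, so 154 per group and 308 in all; 154 / 0.80 = 192.5, so 193 per arm and 386 in all. The sample size is not in question.

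**Set-up.** Let
- c = share of the intervention arm with 3+ sessions, and D = the effect in them;
- q = share with one or two sessions, and f·D = the effect in them;
- the remainder, with no session, have no effect;
- nobody in the control arm receives HomeHealth (an assumption).

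Then:
- Intention-to-treat difference = c·D + q·f·D
- CACE at 3+ = that difference / c = D × (1 + f·q/c)
- CACE at 1+ = that difference / (c + q) = D × (c + f·q) / (c + q)

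**Inputs.** D = 1.85 is used only as a scale. The values of c, q and f are assumptions. The 91% in the Background is attendance per appointment in the feasibility trial, not the share reaching three sessions, so c = 0.91 is only a scenario.

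| c | q | Estimate | f = 0 | f = 0.5 | f = 1 |
|---|---|---|---|---|---|
| 0.91 | 0.05 | 3+ | 1.85 | 1.90 (+2.7%) | 1.95 (+5.5%) |
| | | 1+ | 1.75 | 1.80 | 1.85 |
| 0.85 | 0.10 | 3+ | 1.85 | 1.96 (+5.9%) | 2.07 (+11.8%) |
| | | 1+ | 1.66 | 1.75 | 1.85 |
| 0.70 | 0.20 | 3+ | 1.85 | 2.11 (+14.3%) | 2.38 (+28.6%) |
| | | 1+ | 1.44 | 1.64 | 1.85 |

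One cell in full, at c = 0.85, q = 0.10, f = 0.5: the 3+ estimate is 1.85 × (1 + 0.5 × 0.10 / 0.85) = 1.85 × 1.0588 = 1.96. The 1+ estimate is 1.85 × (0.85 + 0.05) / 0.95 = 1.75.

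**Direction.** At f = 0 there is no bias. At f = −0.25 (partial attendance harms) the 3+ estimate is too low, by 1.4%, 2.9% and 7.1% in the three scenarios.

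**Bracketing.** For f between 0 and 1, (c + f·q)/(c + q) is at most 1 and 1 + f·q/c is at least 1. The expected 1+ estimate therefore lies at or below D and the expected 3+ estimate at or above it (for D above zero). Every row of the table shows this.

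**Against sampling error.** With 154 per arm and no covariate adjustment, the standard error of the 3+ CACE at c = 0.85 is about 5 × √(2/154) / 0.85 = 0.67. At q = 0.10 the bias is 0.05 for f = 0.25 (1.85 × 0.25 × 0.10 / 0.85) and 0.22 for f = 1, or about 0.08 to 0.32 of a standard error.

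A large simulation of four such scenarios agreed with the 3+ formula to within about 0.02 points.

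**The case against.** The strongest reply is that the cut is pre-specified, used consistently and tied to the design of the intervention: three appointments are called a minimum dose and, elsewhere, a therapeutic dose. Progress review, adjustment of goals and habit formation come in the later appointments, and these may matter most for a 12-month outcome. This stands as a reason for defining adherence at three sessions. It does not show that one or two sessions have no effect, which is what the estimator needs.

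A 1+ CACE also answers a different question: the average effect in anyone who starts. That stands. It is why the 1+ estimate should accompany the 3+ estimate and not replace it.

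The likely size is modest, and the analysis is supportive. Both stand. The 29% figure needs 20% partial attenders who gain the full benefit, and the documents support neither.

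Three stronger readings are tempting, and the article does not support them:
- That the CACE is overstated as a matter of fact, or can err only away from zero. This needs benefit from one or two sessions and a non-trivial share of such participants. The article shows neither.
- That action planning and equipment are delivered in the first two sessions. Only the assessment and goal setting are placed there.
- That 3+ is the only CACE result the trial will report. The article defers detail to a statistical analysis plan that is not shown, and other thresholds may appear there. What it does fix is the 3+ cut.

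**Conclusion.** The point holds in conditional form. The one CACE definition in the article rests on no effect of allocation in participants with one or two sessions, and the article's account of those sessions makes that doubtful. If they bring some benefit, the 3+ estimate is too high by f·q/c: 0% to about 29% over the assumed scenarios with f from 0 to 1, and at most about 5.5% if 91% reach three sessions and 5% have one or two. If they bring none, there is no bias; if they harm, the estimate is too low. These figures assume no HomeHealth in the control arm and no effect without any session. The intention-to-treat primary analysis and the sample size are untouched. This is a cheap improvement to a supportive analysis, not a flaw in the trial's main result.

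**What to change.** In the CACE paragraph or the statistical analysis plan:

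1. Keep the 3+ CACE, and state that it assumes no effect of allocation in participants with fewer than three sessions.
2. Add a supportive CACE at 1+ session, labelled as the effect in anyone who starts. The exclusion restriction is more plausible there, because those below the cut had no session. It is not guaranteed, since participants know their allocation.
3. Present the two estimates as bracketing the 3+ complier effect when the benefit of one or two sessions lies between none and that of 3+. Say that this concerns the point estimates in expectation and that each carries its own confidence interval.
4. Report the shares with 0, 1-2 and 3+ sessions beside them.

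The cost is a few sentences, one more run of the same model and one extra supportive estimate to report. HomeHealth workers already record appointments attended, and a descriptive summary of these is already planned, so no new data are needed.

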### Health economic evaluation

Healthcare resource use (contacts with primary, community and secondary care, hospitalisations, procedures and medications) will be extracted from patient medical records. Service resource use not available from files and wider services (e.g. of voluntary sector and social care) will be collected using a modified Client Services Receipt Inventory (CSRI) [63] at 0, 6 and 12 months, asking about the previous 6-months. The CSRI has been modified based on the population in our feasibility study to include the range of services they may use (e.g. podiatry, opticians, hearing aids, dental care, physiotherapy, exercise classes, day care, etc.). Health and social care resource use will be costed using nationally published sources (PSSRU [68], NHS Reference Costs [69] and the British National Formulary [70]). We will additionally ask about unpaid and paid (state and out-of-pocket) carer time for specific activities of daily living, using an adapted iMTA Valuation of Informal Care Questionnaire (iVICQ) [60]. This will be costed as the cost of face-to-face local authority-funded homecare worker time to reflect the fact that if this care were to be reduced homecare workers would be the alternative to unpaid carers providing this assistance.

Intervention costs (including staff training, administration, supervision and delivery) will be included in the costs of the intervention group.

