EQ-5D-5L, ICECAP-O, QALYs and YFC, resource use and costs will be summarised descriptively. Cost-effectiveness acceptability curves and cost-effectiveness planes will be reported to represent the probability that the intervention is cost-effective compared to TAU for a range of cost-effectiveness thresholds for a QALY and YFC gained. Seemingly unrelated regression will be used to account for the correlation between costs and QALYs/YFC. A range of sensitivity analyses will be conducted for any assumptions. Procedures for handling missing data will follow those of the statistical analysis.

We will carry out a budget impact analysis, developing a tool for funders or commissioners to use to assess the yearly costs to their budget of implementing HomeHealth in a range of different commissioning models. Due to the paucity of long-term data upon which to base assumptions regarding effectiveness over time, we will explore alternative scenarios, including: 1) assuming constant effectiveness of the intervention over five years, 2) initial further gains in year 1–2 (if care home moves and hospital admissions are avoided) followed by a depreciation in effect, and 3) a slow decline in effectiveness over time. We will also include the impact of further assumptions such as the grade of intervention delivery staff, training costs and patient case load, taking into account the size and composition of the relevant local population. We will model scenarios for potential costs to the NHS if aspects of the intervention were commissioned by a third sector organisation, or if commissioned as part of publicly funded social care, the impact on local authorities.

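### The cost-effectiveness analysis inherits a complete-case, no-imputation rule that discards partly observed QALYs and costs, although the plan itself allows for 20% attrition

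*Protocol article*

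**What the plan says.** All of the following is in the protocol article.

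- **Missing-data rule.** Statistical methods states that "imputation will not be used" and that "All analyses will be complete case". The reasons given are low missingness in the feasibility study and small expected gains from multiple imputation in randomised trials.
- **Extension to the economic analysis.** Later in the same section, at the end of the paragraph on summarising costs and QALYs: "Procedures for handling missing data will follow those of the statistical analysis".
- **QALYs and capability.** "QALYs will be calculated from the EQ-5D-5L as the area under the curve adjusting for baseline". Table 1 (Outcomes) places EQ-5D-5L and ICECAP-O at baseline, 6 and 12 months. Years of full capability (YFC) are reported over the trial period from ICECAP-O.
- **Costs.** Under Health economic evaluation, health service use comes from medical records. Services not found there, such as voluntary sector and social care, come from the Client Services Receipt Inventory (CSRI) "at 0, 6 and 12 months, asking about the previous 6-months".
- **Joint model.** Costs and QALYs or YFC are analysed by seemingly unrelated regression, with bootstrapped intervals.
- **Primary outcome, for contrast.** The Barthel Index is analysed in a linear mixed model with 6- and 12-month data.
- **Expected loss.** Sample size assumes 20% attrition over 12 months and says of the earlier study: "Attrition was minimal (6%) over 6 months in our feasibility study".

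**The concern.** Leaving out imputation is defensible for the Barthel Index because the mixed model already uses whatever follow-up a participant provides. It gives a valid estimate if missingness depends only on observed data, including the 6-month score.

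The economic totals lack that protection. A QALY and a 12-month cost are each sums over visits. If one term is missing the sum cannot be formed, and regression on the totals, seemingly unrelated or otherwise, omits the participant. The 6-month utility and the 6-month CSRI costs of someone who later drops out are then not used at all. The result is unbiased only if, given the covariates in the model, those with full data are representative of everyone randomised. The 6-month information that could correct for selective dropout is discarded.

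Cost-effectiveness is one of the trial's stated aims, and the Discussion says the economic results are meant to inform commissioners. In a frail older population, people who miss the 12-month visit may well differ in health and service use from those who attend. The economic and clinical results would also rest on different sets of participants, although the plan promises intention to treat for all analyses.

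**Working it through.** **1. Is 20% the plan's own working figure?** Inputs from Sample size: difference 1.85, SD 5, 90% power, 5% significance (taken as two-sided), 1:1 allocation.

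- n per arm = 2 × (1.960 + 1.282)² × 5² / 1.85² = 2 × 10.507 × 25 / 3.4225 = 153.5, so 154 per arm and 308 in total.
- Allowing for 20% attrition: 154 / 0.80 = 192.5, so 193 per arm and 386 in total.

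Both stated totals reproduce exactly, so the trial was sized on 20% of participants lacking a 12-month result.

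**2. How many can enter the incremental cost per QALY?**

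- With a 12-month assessment: 386 × 0.80 = 308.8, about 309.
- Without: 386 − 309 = 77.

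A complete-case QALY needs baseline, 6 and 12 months, so 309 is a ceiling. A missed 6-month visit or an incomplete questionnaire lowers it. The documents give no rate for these, so none is applied here. The article does not say whether the 20% includes deaths. If it does, participants known to have died could be scored and added back.

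**3. How much observed follow-up would be discarded?** The documents do not split the 20% by visit. As an assumption, let loss by 6 months equal that in the feasibility study. The article gives this as 6% in Sample size and as 4% in Background (96% remaining).

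- At 6%: 386 × 0.06 = 23 lost by 6 months; 77 − 23 = 54 seen at 6 but not at 12 months.
- At 4%: 386 × 0.04 = 15 lost by 6 months; 77 − 15 = 62 seen at 6 but not at 12 months.

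On that assumption, 54 to 62 participants would inform the Barthel analysis through their 6-month score but contribute nothing to the cost-per-QALY analysis.

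**4. Does the stated reason fit?** The reason rests on 51 people followed for 6 months, with under 1% missing data and 4% or 6% attrition. The rule is applied to a 12-month total in a trial planned for 20% loss, which is 20/6 = 3.3 to 20/4 = 5 times the feasibility attrition. The 4% and 6% figures should be reconciled, but the conclusion does not depend on which is right.

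**5. Which components does a missed 12-month visit remove?**

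| Component | Source | After a missed 12-month visit |
|---|---|---|
| EQ-5D-5L, ICECAP-O | Assessment | Missing; no 12-month QALY or YFC |
| CSRI services and carer time | Assessment | Missing for months 6 to 12 |
| Primary, community and secondary care, hospitalisations, procedures, medications | Medical records | May still be available |

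The cost total is incomplete rather than wholly lost. The cost–QALY pair is still unusable under complete case, because the QALY is missing.

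**The case against.** **The 20% is deliberately cautious.** The article calls it conservative, and feasibility losses were far smaller. This stands as a caution on size: if attrition is low, the problem shrinks. But the plan cannot rely on low missingness for its analysis rule and on 20% attrition for its sample size. A missing-data rule has to serve the case the trial was sized for.

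**Safeguards already exist.** Baseline predictors of missingness will be examined and added to a supportive model, and the economic section promises sensitivity analyses of its assumptions. The supportive model is written for the primary outcome. Even if carried over, it adds baseline variables only and cannot use a dropout's 6-month utility or costs. The economic sensitivity analyses do not mention missing data.

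**Detail belongs in the analysis plan.** The article says that plan will cover the health economic analysis, and the choice of imputation model can properly wait for it. The rule itself, however, is not left open: the article fixes complete case without imputation.

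**Costs come largely from records.** This stands. It would be too strong to say that a missed visit removes all cost data.

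**A reader might infer that participants who die are excluded.** The documents do not say so. Table 1 collects mortality from medical notes or family report, at the two follow-ups and at any time. Giving zero utility after a known death is scoring, not imputation, so the rule does not forbid it. The article is silent on this. It also gives no mortality rates or utilities, so no size can be put on the effect of excluding deaths.

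**Conclusion.** The concern holds and should be fixed before analysis. The article carries a complete-case, no-imputation rule into an analysis of cumulative QALYs and costs, where that rule discards observed 6-month data that the Barthel mixed model would keep. The reason given does not match the plan's own attrition assumption.

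On that assumption at most about 309 of 386 (80%) enter the incremental cost per QALY and about 77 do not. This counts attrition as having no 12-month assessment, before any participants known to have died are scored back in. The count of 54 to 62 with discarded 6-month data rests on the further assumption that 6-month loss matches the feasibility study.

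The direction and size of any bias in cost-effectiveness cannot be derived from the documents. The primary Barthel analysis is not affected.

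**What to change.** Replace the sentence that ties economic missing-data handling to the statistical analysis with a base case that is valid under missing at random and uses the partial data. Suggested text:

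> The base-case economic analysis will use multiple imputation, carried out separately by arm, of EQ-5D-5L, ICECAP-O and cost components at each visit. The imputation model will include baseline covariates and site, and imputation will be combined with the bootstrap. Participants known to have died will have zero utility and no further costs from the date of death; these values are neither imputed nor dropped. A complete-case analysis will be reported as a sensitivity analysis.

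Limit the general statements on imputation and complete case in Statistical methods to the clinical outcomes, so that the two parts agree.

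The cost is plan wording and extra analyst time, with no change to data collection. The downside is reliance on a missing-at-random model that cannot be verified. The complete-case sensitivity analysis shows how far the result depends on the choice of method.
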